#### Methods in analysis to handle protocol non-adherence and any statistical methods to handle missing data {20c}

The primary analysis will be conducted using the full, imputed analysis set comprising all eligible participants with baseline measures of the focal endpoint and according to the intention-to-treat principles. We also define the per-protocol analysis set comprising all eligible participants with a baseline measure for the focal endpoint and considered compliers according to the definition above.

##### Handling missing data

We will use multiple imputation to address the issue of missing outcome values for both primary and secondary endpoints. Missing values will be imputed using Multivariate Imputation by Chained Equations with relevant baseline values and if available values at other follow-up time-points of the focal endpoint.

### Plans to give access to the full protocol, participant-level data and statistical code {31c}

Trial information is confidential until the final report is submitted to the FOJ. Subsequently, only data from participants who have consented to the independent reuse of their data, beyond the START NOW WebApp trial, may be further employed. The dataset can then be provided by the corresponding author upon reasonable request and in accordance with research collaboration and data transfer guidelines. We plan to publish the code for the main analyses with the corresponding papers as a supplement, upon the journal’s request. If it will not be published as part of the appendix, it will be available upon reasonable request to the corresponding author. The pseudonymized data set will be kept for 10 years in accordance with the Swiss legislation.

### Oversight and monitoring {21}

#### Composition of the coordinating center and trial steering committee {5d}

This is a monocentric study, planned, coordinated, and conducted by the START NOW team of the Child and Adolescent Psychiatric Research Department at the University Psychiatric Clinics Basel. The Principal Investigator oversees the study’s implementation, carried out by the study coordinator and a study team. The study team recruits, obtains informed consent, and ensures the protocol’s compliance in accompanying participating institutions and AYA. The study team holds weekly meetings. The sponsor receives biannual updates on the current status of the study. There is no steering committee or other involved parties.

#### Composition of the data monitoring committee, its role and reporting structure {21a}

Not applicable. Considering the minimal risk associated with both the intervention and the trial, there is no evaluation by an independent data safety and monitoring committee.

#### Adverse event reporting and harms {22}

If a SAE occurs, the research project will be interrupted and (i) the event reported to the principal investigator within 24 h and (ii) the Ethics Committee notified on the circumstances via the *Business Administration System for Ethical Committees* (BASEC) within 7 days according to HRO Art. 21. To ascertain that SAE events are reported without any delay, the Basel study team will contact participating institutions via e-mail at T_1_, in the middle of the intervention phase, at T_2_, at T_3_, and at T_4_.

#### Frequency and plans for auditing trial conduct {23}

The Clinical Trial Unit of the DCR is responsible for data monitoring the study. Throughout the study, three monitoring visits (two interim and one final) are carried out in accordance with an established monitoring plan. The process is completely independent from investigators and the sponsor. For more information refer to the monitoring plan.

#### Plans for communicating important protocol amendments to relevant parties (e.g., trial participants, ethical committees) {25}

All amendments, substantial and non-substantial, will be submitted to the EKNZ and implemented only after obtaining the necessary approval. The study team will undergo training on the revised study protocol and all registries will be updated accordingly. In the event of any changes to the trial, affected participants will be notified, and efforts will be made to obtain their re-consent.

The following substantial amendments were made after the initial registration of the trial to enhance participant engagement and accommodate institutional constraints:

Amendments in June 2022:Revised procedures for quality assurance and trainer support.Revised exclusion criteria to prevent excessive exclusion of potential participants.Introduced participant reimbursement.Decreased the minimum number of participants per institution to 4 to enable participation of smaller institutions.Adjusted randomization timing to minimize waiting periods, facilitating more efficient planning of trainer and staff training sessions based on randomization conditions.Adding email addresses to participant consent to streamline staff workload and align with preferred contact methods.

Amendments in September 2022:

Intervention phase shortened from 12 to 9 weeks to accommodate varying participant lengths of stay.Facilitating participation for adolescents and institutions by allowing multiple consecutive or parallel groups within large institutions (same condition).Adjusted sample size to 150 due to smaller-than-expected group sizes in previous recruitment, with calculations based on groups of 4 participants.All materials were provided in French for the French-speaking part of Switzerland.

Amendments in August 2023:Individual expert interviews instead of group discussions for Trainer Satisfaction to accommodate resource constraints of some institutions and ensure their participation.

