### Assignment of interventions: allocation {16}

#### Sequence generation {16a}

The randomization process will occur at the institutional level when a minimum of four eligible participants were available (gave informed consent and passed screening). Participants will be randomized within fully eligible groups of 4 to 12 individuals, stratified by study site and across 3 conditions. Institutions will be randomized using a pre-generated list, generated using the statistical software R, inaccessible to the research team, and provided and implemented through the DCR at the University of Basel.

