#### Concealment mechanism {16b}

The allocation sequence is solely handled by the Clinical Trial Unit of the DCR and is not accessible to the study team. Upon randomization, allocation will be revealed to the study team members via REDCap. Subsequently, the study team members will inform participating institutions and AYAsn.

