#### Implementation {16c}

Institutional randomization will occur after obtaining consent from at least four eligible participants within an institution. The process will be initiated using a pre-generated list attached to REDCap, which is not visible to the study team. The allocation sequence is generated by the DCR.

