### Assignment of interventions: blinding {17}

#### Who will be blinded {17a}

Not applicable. After randomization, the START NOW study team will inform the participating institution, and consequently, the participants, about their allocation to the respective condition.

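### Consecutive groups in an already allocated institution can be recruited with the arm known, so recruitment bias can enter the primary contrast, and the named sensitivity analysis does not address it

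*Protocol article*

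**What the plan says.** **Trigger.** Sequence generation {16a} states: "The randomization process will occur at the institutional level when a minimum of four eligible participants were available (gave informed consent and passed screening". Implementation {16c} repeats it: "Institutional randomization will occur after obtaining consent from at least four eligible participants within an institution". Four is a minimum, and neither section says that enrolment in the institution ends at that point.

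**Unit.** The same part of {16a} adds: "Participants will be randomized within fully eligible groups of 4 to 12 individuals".

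**Disclosure.** Concealment mechanism {16b} keeps the list from the study team beforehand, but then: "Upon randomization, allocation will be revealed to the study team members via REDCap". Under Who will be blinded {17a}: "After randomization, the START NOW study team will inform the participating institution, and consequently, the participants, about their allocation to the respective condition".

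**Who recruits.** The section on the coordinating center {5d} gives recruitment and consent to the same study team.

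**Later groups.** The September 2022 entry in the amendments section {25} describes "allowing multiple consecutive or parallel groups within large institutions (same condition".

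**Analysis.** Statistical methods {20a} specifies an intention-to-treat mixed model with arm, baseline AFQ-Y and a random intercept for the institution group. Additional analyses {20b} names a per-protocol analysis and, as the sensitivity analysis, a repeat on available cases.

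**The concern.** In a cluster trial, concealing the list protects only those who consent before their cluster's arm is revealed. Anyone enrolled afterwards decides whether to join, and answers the screening questionnaires, with the arm known or knowable. The staff who approach them know it too.

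Here the arms are not equally attractive to join. Under Recruitment {15}, the active arms use the WebApp during the trial, whereas TAU participants, and staff training in TAU institutions, wait until after the second follow-up. Eligibility rests on self-reported cut-offs (Table 1), and the Limitations section itself names poor motivation to take part as a problem. Late recruits in an active arm could therefore differ from late recruits under TAU in motivation, willingness and reported symptoms.

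At stake is the comparison the trial calls confirmatory, on an unblinded self-report outcome. Selection of this kind would be read as an intervention effect, or would mask one.

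**Working it through.** **Step 1. Is the route open?** The rules, set side by side:

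- The institution is randomised with at least four consented and screened participants ({16a}, {16c}).
- Its arm becomes known to recruiters, staff and participants ({16b}, {17a}).
- A large institution may then run a further, consecutive group in that same arm ({25}).
- No section requires members of that further group to have consented before disclosure.

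So the route is open for consecutive groups. The amendment entry is not being set against the current text. It describes a rule in force, and {20a} accordingly models training groups within institutions.

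**Step 2. Does the planned analysis close it?** The random intercept handles correlation within groups, not a systematic difference between arms in who was recruited. Baseline AFQ-Y removes only the part of the difference that this score captures. For someone consented after disclosure, that baseline is itself reported after disclosure. The available-case analysis addresses imputation. The per-protocol analysis selects on sessions completed. Neither separates participants by time of enrolment.

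**Step 3. What size could it have?** The article gives no bias figure to reproduce, and neither input needed for one. The precision follows from the Sample size {14} inputs:

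- Planned total: 78 × [1 + (4 − 1) × 0.2] × 1.2 = 78 × 1.6 × 1.2 = 149.8, which matches the stated 150 (50 per arm).
- Effective n per arm after 20% drop-out and clustering: 50 × 0.8 / 1.6 = 25.
- SD after baseline adjustment with r = 0.80: 13.01 × √(1 − 0.80²) = 13.01 × 0.6 = 7.8.
- Standard error of one contrast: 13.01 × 0.6 × √(2/25) = 2.21 points.

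Let f be the share of an arm recruited after disclosure. Let b be the difference at T3, in SD units of 13.01, that remains after baseline adjustment. Then bias = f × b × 13.01. The type I error below is two-sided at an assumed 0.05. Both f and b are assumptions.

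| f | b | Bias (points) | Type I error |
|---|---|---|---|
| 0 | any | 0 | 0.050 |
| 25% | 0.1 | 0.33 | 0.052 |
| 25% | 0.3 | 0.98 | 0.073 |
| 25% | 0.5 | 1.63 | 0.114 |
| 50% | 0.1 | 0.65 | 0.060 |
| 50% | 0.3 | 1.95 | 0.143 |
| 50% | 0.5 | 3.25 | 0.313 |

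For scale, the planned self-help effect is 0.50 × 13.01 = 6.5 points. Because b is what remains after adjustment, 0.1, 0.3 and 0.5 of the full SD equal 0.17, 0.50 and 0.83 of the residual SD (dividing by 0.6). The lower rows of each block therefore assume strong selection.

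**The case against.** **The first group may be fully protected.** A reader might infer from the minimum of four and the maximum of 12 that a first group is filled up after allocation. The text does not establish this. The phrase "fully eligible groups of 4 to 12 individuals" reads naturally as a group of any size in that range, all consented and screened, which is then randomised. Sample size {14} also reports about four participants per group as observed, so there is little sign of topping up. This objection stands, and that reading is not part of the point.

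**The remaining route is narrow.** Parallel groups may all be formed before allocation. Consecutive groups arise only in large institutions, and {25} does not say when their members consent. Keeping one condition per institution also has a sound rationale, since it avoids contamination between arms. All of this limits how many participants are exposed. It does not close the route, because no rule requires consent before disclosure.

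**The analysis may be in the statistical analysis plan.** {20a} announces a detailed plan, which is not shown, and it may contain a restricted analysis. Its absence from the article is therefore not in itself a fault. The point rests on the enrolment rule, which the protocol does fix, and on the fact that the sensitivity analysis it names answers a different question.

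**Safeguards exist.** The screening cut-offs are the same in every arm and baseline AFQ-Y is adjusted for. Both reduce the risk. Neither measures motivation or willingness to join.

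**Conclusion.** The point holds for consecutive groups. As written, the enrolment rule lets their members be recruited after their arm is known, so recruitment bias can enter the primary contrast, and neither the planned model nor the named sensitivity analysis would reveal it.

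A reader might go further and conclude that the contrast is biased. The documents do not support that: they do not say how many participants, if any, enrolled after disclosure, or whether they differed between arms. If none did, the bias is nil. The 0.33 to 3.25 points in the table illustrate what the rule could allow and are not an estimate. They rest on the assumed f and b, on the planning SD, correlation and intracluster correlation, and on a two-sided 0.05 level inferred from the 95% intervals.

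This is a cheap improvement worth making. It is not a demonstrated flaw in the result.

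**What to change.** Recruitment ended in July 2023 (Trial status), so the remedy lies in analysis and reporting.

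1. State whether members of consecutive groups could consent or be screened after their institution's allocation was disclosed.
2. Derive a flag for each participant, before or after disclosure, from the consent and screening dates and the date on which the institution's allocation was revealed. Data collection {18a} has the study team enter time-points and consent-form data in REDCap, and {16b} reveals the allocation there, so the flag should be derivable without new data.
3. Report numbers and baseline scores by arm and flag. If the after-disclosure cells are empty, the matter is closed.
4. Pre-specify in the statistical analysis plan a sensitivity analysis that fits the primary model only to participants consented and screened before disclosure. If the plan is already final, add the analysis as a dated amendment and say whether it preceded database access.

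Keep the primary model and analysis set as planned. Adding the screening (T0) AFQ-Y and MAYSI-2 scores as covariates should not be relied on to correct the bias, because for late recruits those scores also follow disclosure.

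The cost is one derived variable, one table and a few lines of text. The downside is that the restricted analysis is smaller and less precise, so it should be read by whether its estimate shifts, not by whether it remains significant.

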### Dissemination policy {31}

#### Dissemination plans {31a}

Trial information is confidential until the final report is submitted to the Swiss Federal Office of Justice. Following the final report, the results of this trial will be disclosed completely in international peer-reviewed journals. All interested participants can receive a layman's summary of the results upon request.

## Discussion

This randomized controlled trial aims to investigate the efficacy of a web-based translation of START NOW, promoting PF in institutionalized AYA and addressing implementation barriers in RYC and CI. Within participating institutions, 150 AYA with a need to improve resilience will be randomly assigned at the institution level to one of three conditions (i) a 9-week web-based group training guided by a facilitator, (ii) a 9-week web-based self-help training, and (iii) TAU.

### Limitations

The trial has several limitations. First, challenges to engage institutions and participants arise from limited resources and the lack of motivation to participate in a study. Secondly, we anticipate a high dropout rate due to AYA who are difficult to reach. The lengthy 9-month duration of the trial, influenced by factors such as holidays and relocations, contributes to this expectation. Thirdly, recruitment difficulties also stem from structural variations among institutions, non-participation due to resource constraints on the institutional side, and scheduling challenges during vacations. Additionally, the extended follow-up periods post intervention constitute a fourth challenge that may impact participant engagement. Lastly, self-help interventions and questionnaire adherence exhibit low levels among participants, contributing to the overall limitations. These challenges underscore the necessity for cautious result interpretation.

### Strengths

This trial promises valuable insights into the efficacy of a web-based intervention. By utilizing both a group guided by a facilitator and self-help as comparator groups, our goal is to investigate the optimal level of support. This approach not only explores the efficacy of the intervention but also provides a more comprehensive understanding of the required support levels. Importantly, the trial ensures universal access to evidence-based training for emotional regulation and resilience among AYA, leveraging innovative technologies for program appeal and resource efficiency. All training materials remain accessible online even after the funding period concludes ensuring sustainability. Moreover, the inclusion of French-speaking cantons facilitates broad dissemination of the WebApp. Beyond its inherent effectiveness, the training incorporates a dissemination strategy that empowers both employees and AYA to become trainers, fostering resilience and perceived self-efficacy within the community.

## Trial status

At the time of manuscript submission, all participants are in the follow-up assessment period (T_3_ to T_4_). Recruitment started in March 2022 and lasted until July 2023. Submitting the study protocol earlier was not feasible due to challenges, including staff turnover in the study core team and DCR, as well as multiple revisions influenced by participating institutions and a second language region. The current protocol is version 5 of 28-08-2023. The trial closure is scheduled for March 2024, following the last participant`s completion.

## Data Availability

This study protocol is officially registered with ClinicalTrials.gov (Identifier: NCT05313581; registered on 6 April 2022; last updated on 7 April 2024). Data and materials will be publicly available upon final report to the Swiss Federal Office of Justice.

## Abbreviations

ACT: Acceptance and commitment therapy
AE: Adverse event
AFQ-Y: Avoidance and Fusion Questionnaire for Youth
ARI: Affective Reactivity Index
AYA: Adolescents and young adults
BASEC: Business Administration System for Ethical Committees
CBT: Cognitive behavioral therapy
CD-RISC: Connor-Davidson Resilience Scale
CI: Correctional institutions
CIS: Columbia Impairment Scale
ClinO: Ordinance on Clinical Trials in Human Research
CSQ: Client Satisfaction Questionnaire
DBT: Dialectical behavior therapy
DCR: Department of Clinical Research
EKNZ: Ethikkommission Nordwest- und Zentralschweiz [Ethics Commission Northwestern and Central Switzerland]
eCRF: Electronic Case Report Form
EssenCES: Essen Climate Evaluation Schema
FOJ: Federal Office of Justice
MAYSI-2: Massachusetts Youth Screening Instrument-2
MI: Motivational interviewing
PHQ-4: Patient Health Questionnaire-4
PF: Psychological flexibility
RYC: Residential youth care
SAE: Serious adverse event
SWE: Skala zur Allgemeinen Selbstwirksamkeitserwartung [General Self-Efficacy Expectancy Scale]
TAU: Treatment as usual
TSQ: Trainer Satisfaction Questionnaire
WebApp: Web Application
WHO-5: World Health Organization – Five Well-Being Index
